#### Recruitment

Centres will be recruited across Victoria, New South Wales and South Australia and randomised in matched pairs to receive either the PROMOTE implementation package or online education to support guideline implementation.

### Assignment of interventions

#### Randomisation and blinding

Pairs of centres matched on throughput of stroke patients, level of adherence to guidelines reported to Stroke Foundation, and metropolitan or rural will be randomised to experimental or control (1:1) by an independent statistician. Centres will be notified by the principal investigator of their randomised group following the baseline usual care phase and within 4 weeks of an agreed date before commencing the implementation phase.

#### Blinding

All outcomes will be measured by researchers blinded to centre (cluster) allocation. Statistical analysis will be carried out by a statistician blinded to randomisation.

### Data collection and analysis

Data collection commenced in January 2024 and is ongoing (expected to be completed by August 2026, with results available from December 2026).

#### Data collection

Each participating site will appoint a site coordinator responsible for managing participant flow and overseeing local data collection. Blinded outcome assessors will access data either through secure login (primary outcome) or on-site visits to perform assessments (secondary outcomes). All study data will be stored in site-specific, encrypted, access-restricted Microsoft Teams folders, with de-identified data maintained separately from any re-identification keys, ensuring that only authorised personnel at each site can access their own secure database. At the completion of data collection, the de-identified dataset of each site will be securely transferred to Monash University (sponsor) and entered into a REDCap electronic data capture tool hosted at Monash University.^45
46^

#### Statistical analyses

Intention-to-treat analyses will be conducted. A statistical analysis plan will be finalised prior to locking the study database. For the primary analysis of the binary outcome of whether guideline recommendations were received by the participant or not, a three-level mixed effect logistic regression model with the intervention as independent variable and individual centre and the matched pair of centres used for randomisation as nested random effects will be used. The model will be adjusted for the following pre-specified covariates: baseline participant’s age and FIM score, as well as the cluster case volume and proportion of cases with guideline-recommended care provided during the baseline usual care stage. The intervention effect will be presented as adjusted odds ratio and standardised risk difference with respective 95% CI as per US Food and Drug Administration Guidance for Industry ‘Adjusting for Covariates in Randomized Clinical Trials for Drugs and Biological Products’. Relevant secondary outcomes will be analysed by appropriate mixed-effect regression models with the random effects specified as per the primary analysis adjusted for baseline participant’s age and baseline value of the respective outcome variable.

The economic evaluation will be conducted in accordance with the Consolidated Health Economic Evaluation Reporting Guidelines. The incremental cost-effectiveness ratio (ICER) will be calculated relative to the control group and will be reported as a cost per quality-adjusted life year gained. An ICER below $A 50 000 will be considered cost-effective. Acceptability curves of the probability that an intervention is cost-effective as a function of willingness to pay will also be plotted. Appropriate one-way sensitivity and multivariable uncertainty analyses or modelling will be performed to assess the robustness of results.

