### Design

The PROMOTE trial is a two-arm, cluster-randomised, phase IV trial^30^ with concealed allocation, blinded measurement and intention-to-treat analysis (figure 1). The risk of contamination between intervention and control centres is minimised by the cluster-randomised design, whereby randomisation occurs at the centre level; however, in the event that staff move between an intervention and a control centre during the trial period, this will be documented and considered in the analysis. Randomisation will be undertaken centrally by an independent statistician to ensure allocation concealment, both clusters within each matched pair will be enrolled and complete baseline assessment before allocation to minimise selection bias, and the randomisation schedule will be concealed until immediately prior to the implementation phase to maintain temporal concealment. The trial includes three phases: a baseline usual care phase (12 months); a randomised implementation phase (6 months) during which implementation outcomes are assessed; and a post-implementation usual care phase (6 months) during which clinical outcomes are assessed. Only data from the baseline and implementation phases will be used for the primary analysis. Given the nature of the primary outcome, minimal amount of missing data are anticipated. Subject to the satisfiability of missingness at random assumption, depending on the amount of missing data, either complete case analysis or analysis with multiple imputations with chained equations will be undertaken followed by the sensitivity analysis investigating the plausibility of missingness at random assumption. The details will be reported in the statistical analysis plan finalised prior to the study data lock. During the post-implementation period, patients with stroke will be sequentially recruited at each centre and patient measures will be collected at hospital admission and after 4 weeks of rehabilitation (or at the end of rehabilitation if discharged sooner). Economic outcomes will be measured continuously over the randomised implementation phase. Service delivery costs will be obtained from the centres for each trial phase (ie, to determine the implementation delivery costs).

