#### Eligibility criteria

Clinician participants will be occupational therapists and/or physiotherapists who work on participating wards and prescribe and deliver upper limb rehabilitation. Inpatients with stroke undergoing upper limb rehabilitation will be eligible to participate during the post-implementation phase if they are over 18 years old, have sustained a stroke in the previous 6 months, are able to read and understand spoken English to a level where they can understand the participant information sheet, can complete the consent form with/without an interpreter or next of kin, and have stroke-related difficulty using their upper limb that warrants rehabilitation (ie, have a minimum of 5° active finger or wrist extension and a maximum ability of 30 blocks/min on the Box and Block test).

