#### Outcomes

The primary outcome is the proportion of inpatients with stroke with upper limb impairment who are documented to receive the recommended amount and type of upper limb rehabilitation during their admission. Guideline-recommended care was defined per the Stroke Foundation’s Clinical Guidelines for Stroke Management^11^ as ≥2 hours/day of active upper limb practice^18^ delivered using at least one of the constraint-induced movement therapy, repetitive task-specific training or electrical stimulation for strengthening; operational definitions for each are provided in online supplemental file D.

Secondary outcomes include change in clinician implementation behaviour as measured on a Theoretical Domains Framework questionnaire^38^ collected during baseline and implementation phases. Secondary clinical outcomes will be collected during the post-implementation phase, including change in upper limb ability (end of treatment minus admission) measured using the Box and Block test^39^ and Action Research Arm test.^40^ Health benefits will be estimated using the self-rated quality of life tool, EuroQol 5-Dimensions (EQ-5D-5L)^41^ and a preference-based single index score, using Australian preference weights, will be derived.^42^

Activity-based costing will be used to quantify the economic cost of implementing the interventions as an average cost per patient, inclusive of training, supervision and overall rehabilitation costs for eligible patients. Patient-level costs will be measured in $A and reported from a single reference year based on a societal perspective (including direct and indirect costs). Incremental cost per quality-adjusted life year gained will be estimated from the EQ-5D-5L data (change baseline to 4 weeks) and the total costs of intervention delivery compared across groups. Economic modelling will be used where relevant.

A process evaluation will be undertaken to collect intervention data and understand the use of the PROMOTE package within experimental centres from the perspective of clinicians, managers and people with lived experience. Deductive coding of transcribed interviews will be analysed alongside intervention data and findings will be reported according to the RE-AIM framework (Reach, Effectiveness, Adoption, Implementation and Maintenance).^43^

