## Ethics

Ethical approval was granted through the National Mutual Acceptance Scheme by Alfred Hospital Human Research Ethics Committee (approval number 89725(NMA), 26 April 2023). Each participating centre has obtained ethical approvals from their Institutional Research Ethics Committee (online supplemental file A). The trial was registered at ANZCTR 12623000608662 (2 June 2023). Written informed consent will be obtained from clinician participants prior to randomisation (online supplemental file B), and from patient participants prior to baseline assessment. This study will be conducted in compliance with the principles outlined in the World Medical Association’s Declaration of Helsinki.^47^

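### Clinical outcomes come from patients recruited after centres know their arm, and the fixed secondary covariates leave out time since stroke

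*Protocol article*

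**What the plan says.** All places are in the protocol article.

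- **When centres learn their arm** (Randomisation and blinding): "Centres will be notified by the principal investigator of their randomised group following the baseline usual care phase", before the 6-month implementation phase begins.
- **When the patients enter** (Design): "During the post-implementation period, patients with stroke will be sequentially recruited at each centre". The Outcomes section agrees: "Secondary clinical outcomes will be collected during the post-implementation phase".
- **When they consent** (Ethics): clinicians consent before randomisation. Patients consent at a separate point, "and from patient participants prior to baseline assessment", meaning the patient's own admission assessment.
- **Who is eligible** (Eligibility criteria): patients must "have sustained a stroke in the previous 6 months". Their arm difficulty is bounded by at least 5° of active finger or wrist extension and at most 30 blocks/min on the Box and Block test.
- **How they are analysed** (Statistical analyses): the primary model adjusts for age, FIM, cluster case volume and baseline adherence. The relevant secondary outcomes use mixed models adjusted for age "and baseline value of the respective outcome variable".

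**The concern.** In a cluster trial, randomising centres balances patient mix only if patients are identified before the allocation is known, or in a way that the allocation cannot influence. Neither is assured for the clinical outcomes. By the time these patients are approached, an experimental centre has run a champion-led programme for 6 months and a control centre has not. Who is approached, and who agrees, could differ between arms without anyone intending it. With only 14 centres, chance differences in case mix are also likely.

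The remaining protection is covariate adjustment, and the article fixes that set. Baseline score and age describe how impaired and how old a patient is at admission. They do not describe how far into recovery the patient is. A patient admitted soon after stroke and one admitted months later with the same arm score can be expected to change by different amounts over 4 weeks. If the arms differ in time since stroke, that difference enters the estimated effect on upper limb ability and on EQ-5D-5L. Even without imbalance, the unexplained variation costs precision.

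**Working it through.** **Step 1: timing.** Notification comes before implementation starts, implementation lasts 6 months, and patient recruitment starts after it. The gap between a centre knowing its arm and consenting its first patient is therefore at least 6 months.

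**Step 2: do the stated safeguards reach these patients?**

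| Safeguard in the article | What it protects | Covers post-implementation recruitment? |
|---|---|---|
| Both centres of a pair enrolled and assessed before allocation (Design) | Choice of centres | No |
| Clinician consent before randomisation (Ethics) | Clinician sample | No |
| Blinded assessors and statistician (Blinding) | Measurement and analysis | No |
| Matching on throughput, adherence, metropolitan or rural (Randomisation and blinding) | Centre-level balance | Not directly; none is a patient prognostic factor |
| Sequential recruitment, measurable arm limits (Design, Eligibility criteria) | Discretion over entry | In part |

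The article does not say that the site coordinator who handles participant flow is blinded.

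**Step 3: the plan's own figure.** The article gives no figure for this point. Its sample size figures (ICC 0.05, coefficient of variation 0.99, 17 patients per cluster, 7 clusters per arm) supply a design effect to borrow.

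- Unequal clusters: 1 + ((1 + 0.99²) × 17 − 1) × 0.05 = 2.633, so effective n = 119 / 2.633 = 45.2 per arm.
- For 40% against 70%, a t test with 12 df gives power 0.788 and a Wald test on the log odds ratio 0.805. The stated 0.80 reproduces.
- Equal clusters: 1 + (17 − 1) × 0.05 = 1.8.

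**Step 4: possible size of bias.** All inputs here are assumptions. Bias in SD units = partial effect of the omitted covariate, given age and baseline score, × difference between arms in that covariate.

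| Partial effect (SD per SD) | Shift 0.1 SD | 0.2 SD | 0.3 SD | 0.5 SD |
|---|---|---|---|---|
| 0.1 | 0.01 | 0.02 | 0.03 | 0.05 |
| 0.2 | 0.02 | 0.04 | 0.06 | 0.10 |
| 0.3 | 0.03 | 0.06 | 0.09 | 0.15 |

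**Step 5: effect on the nominal 5% error.** Assume 119 patients per arm for these outcomes, residual SD 1 and a normal test. SE = √(2 × design effect / 119), which is 0.174 at 1.8 and 0.210 at 2.633. Error = 1 − Φ(1.96 − bias/SE) + Φ(−1.96 − bias/SE).

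| Bias (SD) | Error at design effect 2.633 | Error at design effect 1.8 |
|---|---|---|
| 0.02 | 5.1% | 5.15% |
| 0.06 | 5.9% | 6.4% |
| 0.09 | 7.1% | 8.1% |
| 0.15 | 11.0% | 13.9% |

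**The case against.** The strongest reply is that little room for selection remains. The phrase about difficulty that warrants rehabilitation might be read as a clinical judgement, but the same sentence defines it by measurable limits at both ends. Recruitment is sequential and assessors are blinded. All of this stands, and it lowers the risk. It does not settle who is approached or who consents, and the limits restrict current arm function rather than stage of recovery.

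A reader might infer that leaving FIM out of the secondary models contradicts the primary model. The documents do not support that. The primary outcome is receipt of care and has no patient-level baseline value, so a functional covariate is natural there. The secondary models carry each patient's own admission score, which absorbs part of what FIM would add. Nor does the article show that FIM is recorded for the post-implementation patients: it appears for the primary model, whose data come from earlier phases, and as a centre descriptor.

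A reader might also infer that the cost per QALY rests on the same covariate set. The economic evaluation has its own paragraph, with its own sensitivity and uncertainty analyses, and no covariates are fixed there.

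Finally, the magnitudes are assumed. That is correct: the article gives neither the distribution of time since stroke nor its effect on change, and 6 months is a ceiling, not a typical value. The 11 to 14% error rates need the top of both assumed ranges.

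The point is still more than a detail left to the analysis plan, because the article itself names the secondary covariates.

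**Conclusion.** The concern holds in a limited form. Patients for the clinical outcomes are recruited after their centre knows its arm, no stated safeguard fully covers that step, and the fixed covariate set omits time since stroke, which can vary up to 6 months.

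The likely harm ranges from negligible to moderate: 0.01 to 0.15 SD of bias, in a direction that cannot be predicted, if the omitted covariate has a partial effect of 0.1 to 0.3 SD per SD and the arms differ by 0.1 to 0.5 SD. The error rates rest further on 119 patients per arm and a design effect of 1.8 to 2.633, both borrowed from the primary outcome.

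A reader might go further and conclude that recruitment is, or will be, selective, or that the trial's main result is at risk. The documents show only that the opportunity exists. The primary outcome is a record audit using the baseline and implementation phases and is not touched by this point.

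**What to change.** Before database lock, while the analysis plan is still open and before outcomes by arm are seen:

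1. Add time since stroke at admission, for example as log days, to the pre-specified covariates for Box and Block, Action Research Arm and EQ-5D-5L, beside age and the baseline value.
2. Confirm whether admission FIM is recorded for the post-implementation patients. If it is, add it too.
3. Report both variables by arm.

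Eligibility already requires establishing when the stroke occurred, so time since stroke should need no new data collection. The cost is one or two extra covariates, a change of wording and a little more analysis. Both covariates are patient-level, so they use almost none of the limited centre-level information.

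Adjustment corrects measured imbalance only. Counts of patients screened, eligible and consented by arm, where logs exist, would let readers judge the rest.

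### The A$50,000-per-QALY verdict is applied to an ICER built on 4 weeks of health gain, so it can pass only if the extra cost per patient is at most a few hundred dollars

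*Protocol article*

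**What the plan says.** Three parts of the Protocol article bear on this point.

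- **Health side.** Under Outcomes, the incremental cost per QALY is to be "estimated from the EQ-5D-5L data (change baseline to 4 weeks) and the total costs of intervention delivery compared across groups". The Design section confirms the schedule: "patient measures will be collected at hospital admission and after 4 weeks of rehabilitation (or at the end of rehabilitation if discharged sooner". The observed window is therefore 4 weeks at most, and shorter for patients discharged early.
- **Cost side.** Outcomes describes the implementation cost "as an average cost per patient, inclusive of training, supervision and overall rehabilitation costs for eligible patients". Under Interventions, the package includes a champion, a multimodal education programme and equipment such as stimulation machines and treatment tables.
- **Decision rule.** Statistical analyses states: "An ICER below $A 50 000 will be considered cost-effective". It also plans acceptability curves over willingness to pay.

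Modelling appears twice. Outcomes says: "Economic modelling will be used where relevant". Statistical analyses says: "Appropriate one-way sensitivity and multivariable uncertainty analyses or modelling will be performed to assess the robustness of results". Neither sentence gives a horizon or says that the threshold will be applied to a modelled result.

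**The concern.** A cost-per-QALY threshold is informative only if costs and health are counted over a period long enough for the benefit to appear. Here the package is paid for through training, supervision and equipment, while the only health input named for the ratio is a change over 4 weeks. The Introduction motivates the trial partly by long-term independence, yet any benefit after week 4 has no value in the ratio that the article names.

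The Abstract puts cost-effectiveness in the stated aim. If the rule is followed as written, a package that improves quality of life could be reported as not cost-effective because of the length of the window, not because of its value.

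**Working it through.** The article derives no figure on this point that could be reproduced. The A$50,000 cut is stipulated, and neither a cost nor an expected utility difference is given.

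**Inputs from the article:** threshold A$50,000 per QALY (Statistical analyses); window 4 weeks = 4/52 = 0.0769 year (Outcomes, Design).

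**Assumption:** a between-arm utility difference *d* at 4 weeks, equal utilities at baseline, and *d* ranging from 0.05 to 0.20.

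**Step 1: QALY gain over 4 weeks.**
- Linear accrual (area under the curve): 0.5 × *d* × 4/52 = 0.0385*d*.
- Upper bound, full difference from day one: *d* × 4/52 = 0.0769*d*.

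**Step 2: largest extra cost per patient that passes** = 50,000 × QALY gain.

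| *d* | QALY gain, linear | Cost limit, linear | Cost limit, upper bound |
|---|---|---|---|
| 0.05 | 0.0019 | A$96 | A$192 |
| 0.10 | 0.0038 | A$192 | A$385 |
| 0.20 | 0.0077 | A$385 | A$769 |
| 1.00 | 0.0385 | A$1,923 | A$3,846 |

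The last row is the whole distance from death to full health.

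**Step 3: the same relation read the other way.** The utility difference needed to pass at extra cost *c* is *c* / (50,000 × 0.0385) with linear accrual, or *c* / (50,000 × 0.0769) at the upper bound.

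| Extra cost per patient | *d* needed, linear | *d* needed, upper bound |
|---|---|---|
| A$500 | 0.26 | 0.13 |
| A$1,000 | 0.52 | 0.26 |
| A$2,000 | 1.04 (not attainable from death to full health) | 0.52 |

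**Step 4: does the rule separate benefit from no benefit anywhere?** Yes, inside the band. At an extra cost of A$100, *d* = 0 fails. With *d* = 0.10 the ICER is 100 / 0.00385, about A$26,000, which passes.

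**Step 5: how much the horizon matters.** Take *d* = 0.10 with linear accrual to week 4, then extend to 52 weeks:
- Linear fade to zero by week 52: 50,000 × 0.10 × (0.0385 + 0.5 × 48/52) = A$2,500, which is 13 times the 4-week limit of A$192.
- Gain held to week 52: 50,000 × 0.10 × (0.0385 + 48/52) = A$4,808, which is 25 times that limit.

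Over *d* = 0.05 to 0.20 the 4-week limit itself changes only fourfold, so the choice of horizon moves the limit more than the effect size does across this range.

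**The case against.** The strongest reply is that the Outcomes sentence names the observed utility data, not a time horizon. The article never calls the 4-week ICER its base case, it permits modelling in two places, and horizon and extrapolation rules are usually set in an analysis plan. That plan is still to be finalised. Part of this stands: nothing in the article forbids a longer horizon. But the article does more than stay silent. It says what the ratio is estimated from and sets a pass mark for the ratio, while modelling is conditional in one place and a robustness check in the other. The acceptability curves do not close the gap, because they vary willingness to pay and not the horizon.

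A second reply is that the incremental cost may be small or negative: champions come from existing staff, and costs are taken from a societal perspective. This also stands. A package that saves money and improves health passes at any horizon.

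A reader might go further and infer that the rule cannot tell an effective package from an ineffective one, that the cost difference alone decides the verdict, or that the verdict is close to a coin toss. The documents do not support this. The rule does discriminate when the extra cost lies within a few hundred dollars, and no cost is given that would place the trial outside that band. Any simulated rate of false verdicts needs cost and utility standard deviations and a post-implementation sample size, none of which the article states. A 50% pass rate for a cost-neutral package with no effect follows from symmetry under any point-estimate rule, and is not caused by the 4-week window.

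**Conclusion.** The concern holds in a limited form. Followed as written, the A$50,000 rule judges an ICER with at most 4 weeks of health gain. It passes only up to about A$96 to A$385 extra per patient for utility gains of 0.05 to 0.20 with linear accrual, or A$192 to A$769 if the gain is immediate. Above that range, a package with a true gain of this size would be declared not cost-effective.

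The arithmetic rests on the article's threshold and window. The utility gains and the accrual shape are assumptions, shown as ranges. Whether the actual extra cost falls above or below these limits is unknown. The point concerns a secondary outcome and leaves the primary analysis untouched, but it should be settled before the analysis plan is final, because a horizon chosen after the results are seen could decide the verdict.

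**What to change.** In Outcomes and Statistical analyses, and in the analysis plan:

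1. Report the 4-week within-trial ICER descriptively, without the A$50,000 verdict.
2. Pre-specify the already permitted model as the analysis that the threshold and the acceptability curves judge. State one horizon, for example 12 months.
3. Spread training and equipment costs over the same horizon.
4. Name one deciding scenario, for example linear fade of the 4-week utility difference to zero. Without a named scenario, a cost between the two limits in Step 5 would have no defined verdict.
5. Show the gain-held and 4-week-only results as sensitivity analyses.

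This costs wording and a simple extrapolation model on data already being collected, with no new patients or visits. The downside is that the verdict then depends on an explicit assumption about persistence after week 4, which the trial does not observe. The sensitivity analyses make that dependence visible but do not remove it.

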#### Sample size

With a baseline adherence to guidelines of 35%,^44^ assuming control centres will increase this adherence to 40% and experimental centres to 70%, that is, an absolute difference of 30%, we will recruit 14 centres (clusters) evenly split between experimental and control arms. The intraclass correlation coefficient (ICC) observed in our pilot was <0.01.^26^ Assuming more conservative settings of ICC=0.05, a coefficient of variation of cluster sizes of 0.99 and no correlation between baseline measures and the outcome, recruiting 7 clusters per arm with an average 17 patients per cluster (a total sample size of 238 patients, 119 per arm) would yield power of 0.8 to observe an absolute difference of at least 30% with a two-sided alpha=0.05.

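### The A$50,000 ICER rule is correct only when QALYs are gained; for an estimated QALY loss it either reverses the verdict or gives none

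*Protocol article*

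**What the plan says.** The Statistical analyses section of the Protocol article defines the ratio and then the verdict. The ICER "will be calculated relative to the control group and will be reported as a cost per quality-adjusted life year gained". The next sentence is the decision rule: "An ICER below $A 50 000 will be considered cost-effective". It sets no condition on the sign of the cost difference or of the QALY difference. The text moves straight from the verdict to the curves, with no qualification in between: an ICER under the threshold "will be considered cost-effective. Acceptability curves of the probability that an intervention is cost-effective" come next.

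The Outcomes section gives the source of the denominator: "Incremental cost per quality-adjusted life year gained will be estimated from the EQ-5D-5L data (change baseline to 4 weeks"). The numerator is the total cost of intervention delivery, compared across groups.

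Two other statements bear on the point. "Acceptability curves of the probability that an intervention is cost-effective as a function of willingness to pay will also be plotted", and "The economic evaluation will be conducted in accordance with the Consolidated Health Economic Evaluation Reporting Guidelines". One-way sensitivity analyses and multivariable uncertainty analyses or modelling are also planned. No sentence mentions dominance, a negative ratio or a QALY loss.

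**The concern.** A ratio loses the signs of its parts. A package that costs more and yields fewer QALYs has a negative ICER, and so does a package that costs less and yields more. Both lie below A$50,000, yet one is dominated and the other dominant. Where both differences are negative the ratio is positive, but a high value is then the favourable one.

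Cost-effectiveness is part of the stated aim in the Abstract, and the ICER sentence is the only place where a verdict is defined. If the QALY difference is estimated below zero, the rule as worded gives the wrong answer or none. The outcome is not remote, because 4 weeks of follow-up leaves a QALY difference close to zero.

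**Working it through.** **The plan's own figure.** A$50,000 per QALY is a chosen threshold, not a derived number, so there is nothing to reproduce.

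**Step 1: when is the rule right?** Let ΔC and ΔQ be the cost and QALY differences (PROMOTE minus control). Incremental net monetary benefit is INMB = 50,000 × ΔQ − ΔC, and the package is worth its cost at this threshold if INMB > 0. The rule is ΔC/ΔQ < 50,000.

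- If ΔQ > 0, multiplying by ΔQ gives ΔC < 50,000 × ΔQ, which is INMB > 0. Rule and net benefit always agree.
- If ΔQ < 0, multiplying by ΔQ flips the inequality: ΔC > 50,000 × ΔQ, which is INMB < 0. The rule then passes exactly the packages that it should fail.

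**Step 2: numerical cases.** The values are illustrative and are not in the protocol. Only the signs and the ratio matter. A QALY difference of 0.02 is larger than 4 weeks would be likely to produce.

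| Case | ΔC (A$) | ΔQ | ICER | Passes rule? | INMB (A$) | Agree? |
|---|---|---|---|---|---|---|
| Costs more, gains QALYs | +1,000 | +0.04 | 25,000 | yes | +1,000 | yes |
| Costs more, gains QALYs | +1,000 | +0.01 | 100,000 | no | −500 | yes |
| Dominant | −1,000 | +0.02 | −50,000 | yes | +2,000 | yes |
| Dominated | +1,000 | −0.02 | −50,000 | yes | −2,000 | **no** |
| Small saving, loses QALYs | −500 | −0.02 | 25,000 | yes | −500 | **no** |
| Large saving, loses QALYs | −2,000 | −0.02 | 100,000 | no | +1,000 | **no** |

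The dominant and dominated cases share the same ICER, so the ratio alone cannot separate them.

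**Step 3: how near zero is ΔQ?** A utility difference of 0.05 held for the full 4 weeks is 0.05 × 4/52 = 0.0038, or about 0.004 QALY.

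**Step 4: how likely is an observed loss?** This is an illustration only.

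- *From Sample size:* 119 per arm, mean cluster size 17, coefficient of variation of cluster size 0.99, planning ICC 0.05 (pilot ICC below 0.01). All of these concern the adherence outcome. EQ-5D-5L comes from patients recruited after implementation, for whom the article gives no number.
- *Assumed:* SD of the utility measure 0.25; ICC for utility 0.01 to 0.05; true utility gain 0.05, 0.02 or 0.

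Design effect = 1 + ((1 + 0.99²) × 17 − 1) × ICC = 1 + 32.66 × ICC, which is 1.33 at ICC 0.01 and 2.63 at ICC 0.05.

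SE of the utility difference = 0.25 × √(2 × design effect / 119), which is 0.037 and 0.053.

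P(observed loss) = Φ(−gain / SE):

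| True utility gain | ICC 0.01 | ICC 0.05 |
|---|---|---|
| 0.05 | 9% | 17% |
| 0.02 | 30% | 35% |
| 0 | 50% | 50% |

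For a positive true gain, fewer EQ-5D-5L patients than 119 per arm would raise these chances and more would lower them.

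**The case against.** The strongest reply is that the article supplies its own limit. The ICER is reported per QALY gained, the threshold sentence follows at once, and the Outcomes section uses the same expression. A package that loses QALYs has no cost per QALY gained to set against A$50,000. This is a fair reading, and on it the rule is correct throughout its range. It does not close the gap: the expression is also the ordinary unit of an ICER, and if the rule covers gains only, the article states no verdict for a loss.

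Second, the acceptability curves are conventionally built on net benefit and would then show a dominated package as unlikely to be cost-effective. That would be a useful check, but the article does not say how the curves will be built and attaches no decision to them. The reporting guideline is invoked only in general terms.

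Third, this is a condensed article, and the handling of dominance may be set out in a fuller plan that is not shown. That stands as a reason to treat the point as minor. It does not change the fact that the published rule is stated without a sign condition.

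Three stronger readings are tempting and are not supported:

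- *That the trial will call a dominated package cost-effective.* The wording per QALY gained and the other planned outputs make that far from certain.
- *That the rule works only when both differences are positive, or fails for every negative ICER.* It is also right for a dominant package.
- *That 9–50% is the chance of a wrong conclusion.* It is the chance of an observed QALY loss under assumed inputs and a borrowed sample size. A wrong verdict also requires that the rule be applied literally. Any economic modelling could also change the estimate.

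**Conclusion.** The point holds in a limited form. Taken literally, the rule is correct for any QALY gain and reversed for any QALY loss; this follows from algebra and needs no assumption. Taken charitably, it is silent on a loss. A loss is a realistic result because the QALY difference is measured over 4 weeks: a 0.05 utility difference is worth only about 0.004 QALY. The illustrative chances (about 9–17%, 30–35% and 50% for true utility gains of 0.05, 0.02 and 0) rest on an assumed SD of 0.25, assumed ICCs of 0.01 to 0.05, and the adherence sample size and cluster-size variation carried over to a different group of patients. Severity is minor: one secondary economic verdict is concerned, and the primary outcome and its analysis are not touched.

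**What to change.** Base the verdict on incremental net monetary benefit at the threshold already chosen: the package is considered cost-effective if 50,000 × QALY difference − cost difference is above zero, with uncertainty estimated in a way that respects the matched pairs and centres. Report the ICER together with the signs of both differences, and write dominant or dominated in place of a negative ratio. State that the acceptability curves are built on the same net-benefit quantity, so that the two outputs cannot disagree.

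This costs a sentence or two in the protocol and the health-economic analysis plan. It needs no new data, and it can be done before the database is locked, which is when the article says the statistical analysis plan will be final.
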